## Abstract

**Background:**

Community-based behavior change interventions are a common approach to Water, Sanitation, and Hygiene (WASH). Yet, published evaluations of how these interventions work in district-wide approaches are rare.

**Objective:**

This study reports the baseline characteristics and study design for a trial assessing the effectiveness of a district-level Community-led Total Sanitation (CLTS) intervention compared to the additional integration of local care groups (CG) on sanitation coverage and use and hygiene behaviors in Chiradzulu District, Malawi.

**Methods:**

This study is a controlled before-and-after trial with 2 treatment arms and a control group. Clusters are rural villages in 3 traditional authorities (TAs). One arm will receive CLTS and the CG model (CLTS+CG group), one arm CLTS only (CLTS group), and one group will serve as the control. The trial is part of the wider WASH for Everyone (W4E) project, led by World Vision Malawi that aims to expand access to WASH services across the entire district by 2025. Study participants were selected from the 3 TAs. Systematic sampling procedures were used to select 20 households per cluster with a total of 1400 households at both baseline and end line. The primary outcome is sanitation coverage. Secondary outcome measures include sanitation use, safe disposal of child feces, observed handwashing facility, and Sanitation-related Quality of Life Index (SanQoL-5).

**Results:**

The baseline observations indicate a balanced distribution of potential demographic confounders in the trial arms with a slight variation on some WASH proxy measures. We noted the low coverage of handwashing facilities with soap and water in all 3 arms: 8% in the CLTS group, 4% in the CLTS+CG group, and 4% in the control group. There was a marginal variation in handwashing practices among the study arms with 3% of individuals handwashing with soap and water in the CLTS group, 5% in the CLTS+CG group, and 2% in the control group. Sanitation coverage also varied among the study arms at baseline as 83% of households had access to unimproved sanitation in the CLTS group, 70% in the CLTS+CG group, and 81% in the control group.

**Conclusions:**

Results from this trial will provide evidence on whether the CLTS+CG approach is effective at improving sanitation and hygiene practices in the W4E program area compared to CLTS alone and no intervention, as well as inform implementing partners on future interventions in Chiradzulu District, Malawi. The results are expected to be published in 2025.

**Trial Registration:**

ClinicalTrials.gov NCT05808218; https://clinicaltrials.gov/study/NCT05808218

**International Registered Report Identifier (IRRID):**

RR1-10.2196/68280

## Introduction

Globally, it is estimated that 3.6 billion people lack access to basic sanitation services and 494 million people practice open defecation (OD), with the highest rates of OD in Sub-Saharan Africa [1]. Consequences of OD include fecal contamination of drinking water sources and food, which contributes to a high burden of diarrheal diseases and child stunting, adversely impacting health and socioeconomic development [2,3]. Further, OD and inadequate sanitation disproportionately affect the safety and dignity of women, girls, and marginalized groups [3-6], as well as other aspects of quality of life [7]. Efforts by governments and other sanitation stakeholders to eliminate OD, such as the provision of subsidized latrines to households combined with hygiene and health education programs, have failed to make adequate sustained progress [8,9]. Behavior-centered interventions have been associated with improved uptake of sanitation interventions, but more evidence is needed to assess their impact on behavioral outcomes when implemented in combination with one another.

Our study focuses on 2 specific community-led interventions widely used in the Water, Sanitation, and Hygiene (WASH) sector. The first is Community-Led Total Sanitation (CLTS), an approach to sanitation behavior- change centered on community-wide behavior change and community self-enforcement in rural settings [9]. Introduced in Bangladesh in 2009 and now adopted globally, the major goal of CLTS is to mobilize communities to construct and use latrines to end OD [9]. CLTS uses 3 phases to leverage social and emotional drivers to “trigger” a change in people’s mindsets towards OD [10]. Evidence on the efficacy of CLTS is mixed. Certain studies highlight that CLTS only generates significant short-term impact for reducing OD through increased latrine coverage and use [9,11-14]. CLTS implementation factors, such as triggering session attendance, the number of supportive community leaders, participants’ anticipation to receive an incentive, and the number of follow-up visits, have been reported to significantly influence latrine coverage [15]. The second is the care group (CG) model which relies on a multiplier effect to reach a high number of households in a community at a low cost through the development of a supportive network of peer-to-peer counseling [16]. The CG model is a well-tested program for the delivery of health interventions in rural communities, historically focusing on maternal and child health [16-19]. A total of 23 nongovernmental organizations (NGOs) have implemented the CG model across 27 countries, including Malawi [17,19]. Studies have documented the effectiveness of the CG model in increasing coverage of child survival interventions and reducing under-five mortality [18-20]. However, despite their clear alignment, studies of the effectiveness of CGs as they relate to WASH interventions are limited.

In Malawi, communities struggle to sustain 100% latrine coverage after attainment of Open Defecation Free (ODF) status [21]. This has been attributed to a number of factors, including the lack of involvement of marginalized and disadvantaged people, the use of low-quality building materials, lack of technical support, and improper program implementation [14,22]. To achieve high and sustained latrine coverage and behavior change, it is essential to address all physical and contextual factors that directly relate to long-term CLTS success. The Government of Malawi adopted CLTS as one of its official approaches to sanitation in 2008 [23]. The Government formally adopted the CG model in 2011 as an operational framework for the Scaling Up Nutrition (SUN) Strategy [24]. However, little is known about how effective the CG model can be in promoting wider community health benefits, such as improved sanitation. Models to promote sustained reductions in open defecation and improved sanitation outcomes through a combination of behavior-centered intervention need to be tested and adopted to support long-term positive health outcomes.

This study aims to assess the effectiveness of CLTS combined with the CG model on sanitation coverage and use and hygiene behaviors in Chiradzulu District, in rural Malawi, compared to CLTS alone or with no intervention. The study objectives are to assess: (1) how the 2 interventions compare with one another for improving sanitation coverage and use, and (2) whether the 2 interventions are individually more effective than no intervention at all.

## Methods

### Study Setting and Population

The study is implemented in Chiradzulu District, Malawi (Figure 1). Chiradzulu District is situated in the southern region of Malawi and is subdivided into 10 administrative regions, or traditional authorities (TA). The Malawi 2015-2016 Demographic and Health Survey (DHS) indicated that 52% of the population has access to improved sanitation. According to the National Statistical Office, in 2019, 93% and 10% of the households in Chiradzulu District had access to safe water and improved sanitation facilities, respectively. OD rates in Malawi and Chiradzulu District are 6% and 7%, respectively [25]. Given this low level of coverage, Chiradzulu District is the target of a 3-year (2021-2024) district-wide water, sanitation, and hygiene program, known as WASH for Everyone (W4E), implemented by World Vision and Water for People, alongside which this trial is embedded.

**Figure 1 figure1:**
[figure not shown]
(A) Map of Malawi with Chiradzulu District in red, and (B) Map of Chiradzulu District with W4E study areas with TA Chitera (CLTS+CG group) in red, TA Ntchema (CLTS only) in yellow, and TA Nkalo (control) in green. CG: care group; CLTS: community-led total sanitation.

### Study Design

The study design is a controlled before-and-after (CBA) trial with 2 treatment arms (each with 20 villages or clusters) and a control group (30 villages; Figure 2; Multimedia Appendix 1). CBA intervention designs are a nonrandomized approach used to evaluate the impact of interventions [26]. The advantages and disadvantages of the CBA study designs, also known as nonrandomized cluster-controlled trials, have been discussed elsewhere [27]. In this study, TAs are the unit of intervention assignment and villages (clusters) are the unit of analysis. [28] In our study, we selected 3 TAs (Figure 1) in Chiradzulu District, Malawi. TAs are 4th-level administrative units, with an average population of 34,000 in Chiradzulu [29]. Details on the program intervention are described below. For our trial, we selected 2 out of the 5 TAs scheduled to receive the full W4E intervention during the second year of program implementation to align with our implementation. We selected the 2 TAs with the closest match in population and estimated sanitation coverage from previous surveys. In discussion with program partners, one TA was assigned to receive the CLTS intervention, and one TA was assigned to receive the CLTS+Care Group intervention. We selected a third TA from the 3 TAs scheduled to receive the WASH for Everyone intervention in the third year of program activities as a control group for our study (Figure 2). The control TA was selected based on generally similar population and sanitation coverage measures and lack of contiguous borders with the 2 intervention TAs. TAs are the unit of intervention assignment for our study. Within each TA, villages serve as the specific study clusters which are the primary sampling units for data collection.

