### Sample Size

Sample size calculations were based on the minimum detectable effect (MDE) to assess changes in sanitation coverage, the primary outcome measure, at the project end line. Data for all parameters used in sample size calculations were drawn from the baseline survey conducted by World Vision before the implementation of the W4E project between January and April 2021. For the MDE calculation, we assumed a 2-tailed test with a significance level of 0.05 and a power of 0.8. We assumed a conservative intracluster coefficient of 0.1 [30]. As baseline data indicates that the average percentage of households with at least unimproved sanitation coverage across Chiradzulu District was 67%, power calculations assumed a total enrollment of 20 intervention clusters in each TA receiving interventions and 30 clusters selected from the control arm of the study. Assuming an average of 20 households surveyed per selected cluster results in an MDE of 0.136 or an average difference of 13.6 percentage points in sanitation coverage (relative change in coverage of 19%) between either arm of intervention clusters and the control cluster. Therefore, the study aims to recruit a total of 1400 households (CLTS+CG: n=400; CLTS only: n=400; Control: n=600; Figure 2) at each data collection round.

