### Analysis

Statistical analysis will be carried out at the individual or household levels with appropriate adjustments for clustering within villages (and within households for individual-level outcomes). Data will be analyzed according to the TA and intervention assignment irrespective of whether the intervention was taken up fully, partly, or not at all. Since this is an effective study, only an intention-to-treat dataset will be maintained.

The primary estimates of the effectiveness of the intervention on primary and secondary outcomes will be based on a difference-in-difference analysis and models adjusted for design variables alone (TA, village population above or below TA-specific median); a fixed effect for village size (above or below the median) will be included in the model. All models will include a dummy variable for the treatment arm (ie, CLTS, CLTS+CG, or control) and data collection round (baseline and end line) as well as the interaction term of those 2 variables.

To account for the clustering of observations, hierarchical mixed-effects models will be used for all analyses. For household-level outcomes or outcomes where there is only one respondent per household, mixed effects models will account for clustering by including a random effect at the village level. For outcomes with multiple respondents or data points per household (specifically sanitation use, and hand washing behavior), an additional random effect will be added at the household level.

All analysis of primary and secondary outcomes will be based on the difference-in-difference approach. The regression coefficient of the interaction term between the treatment arm and the data collection round will be used as the primary effect measure. For binary outcomes measure, we will use melogit with robust SEs and regression coefficients exponentiated to estimate an odds ratio (OR). For continuous outcomes, we will use meglm, with identity link and Gaussian family.

The results will be presented with 95% CIs. Analyses will report on ORs and 95% CIs of each treatment arm compared to the control as well as the CLTS alone compared to CLTS+CG. Secondary outcomes include the following:

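### Each arm is a single TA, so the effect cannot be separated from TA-specific change, and the village-clustered CIs and MDE hold only for the difference between three named TAs

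*Protocol article*

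**What the plan says.** **Assignment.** Study Design separates the two levels: "In this study, TAs are the unit of intervention assignment and villages (clusters) are the unit of analysis". For the intervention arms, "one TA was assigned to receive the CLTS intervention, and one TA was assigned to receive the CLTS+Care Group intervention". For the control, "We selected a third TA from the 3 TAs scheduled to receive the WASH for Everyone intervention in the third year of program activities". The Figure 1 caption and Description of the Intervention name them: Chitera is CLTS+CG, Ntchema is CLTS, Nkalo is control.

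**Analysis.** The primary estimates are a difference-in-difference from "models adjusted for design variables alone (TA, village population above or below TA-specific median"). All models also carry arm, round and arm by round, and the interaction coefficient is the effect measure. Clustering is handled by a village random effect, plus a household effect where a household gives several data points. Adjustment for Covariates names village size as the only design variable and leaves TA out.

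**Sample Size.** The calculation uses a two-sided 5% test with 80% power. On clustering, it says: "We assumed a conservative intracluster coefficient of 0.1". With 20 villages per intervention arm, 30 control villages and 20 households per village, on a base of 67%, the stated MDE is 0.136.

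**Intended claim.** The abstract's Conclusions promise evidence on "whether the CLTS+CG approach is effective at improving sanitation and hygiene practices in the W4E program area". The Discussion repeats this. It lists purposive, non-random selection as a limitation but does not mention that each arm is one TA.

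**The concern.** With one assigned unit per arm, anything that shifts a whole TA between the 2023 and 2024 surveys enters the arm-by-round coefficient and is reported as intervention effect. The villages in that TA share the shift, so adding villages or households does not average it out, and a village random effect or village-level ICC does not see it.

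The article itself makes area-level influences plausible. The Discussion says that other TAs in the district went back to open defecation after reaching ODF status, and that other NGOs were working on water supply in the study areas just before baseline.

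What is at stake is the meaning of the intervals. They will be read as the uncertainty about whether CLTS or CLTS+CG works, and used to advise partners on later programmes. They measure only the uncertainty from sampling villages and households within three particular TAs.

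**Working it through.** **1. Reproduce the stated MDE.** Inputs from Sample Size: p1 = 0.67, two-sided alpha 0.05, power 0.80, ICC 0.1, 20 households per village, 20 against 30 villages.

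- Design effect = 1 + (20 − 1) × 0.1 = 2.9.
- Effective n: control 600/2.9 = 206.9; intervention 400/2.9 = 137.9.
- Two-proportion formula with pooled variance under the null: MDE = 1.96 × SE0 + 0.842 × SE1.
- At p2 = 0.8058, the pooled proportion is 0.7243, SE0 = 0.0491 and SE1 = 0.0469.
- MDE = 0.0963 + 0.0395 = 0.1358, against 0.136 stated.

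The figure reproduces with village clustering as the only between-cluster variance. It contains no TA component, and it is a single-round comparison at end line.

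**2. Can TA be fitted beside arm?** The fixed effects were coded for three TAs, two rounds and two village-size strata, and the rank of the design matrix was taken.

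| Model | Columns | Rank |
|---|---|---|
| arm, round, arm × round, village size | 7 | 7 |
| the same plus TA | 9 | 7 |
| the same plus TA and TA × round | 11 | 7 |

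TA adds nothing to arm. The arm dummy already removes constant differences between TAs, so software would drop the TA terms and no estimate would change. The third row is the important one: TA-specific change cannot be distinguished from the effect measure.

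**3. Can TA-level variance be estimated?** 3 TAs − 3 arms = 0 degrees of freedom. No analysis of these data can supply it.

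**4. Consequence for the CIs.** Let SE be the village-level standard error of a planned contrast on its own scale (log odds for binary outcomes). Let s be the SD of a TA's own change between rounds on that scale, independent between TAs. As an estimate of the effect of the approach, the contrast has variance SE² + 2s². The planned CI uses SE² only. Its coverage is therefore 2Φ(1.96/k) − 1, with k = √(1 + 2(s/SE)²).

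The documents do not give s. The ratios below are assumptions:

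| s/SE (assumed) | k (correct width / planned width) | Coverage of nominal 95% CI |
|---|---|---|
| 0 | 1.00 | 95% |
| 0.25 | 1.06 | 94% |
| 0.5 | 1.22 | 89% |
| 1 | 1.73 | 74% |

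Only s = 0 gives nominal coverage. The same holds for the stated 80% power at 13.6 points.

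**The case against.** **The design is disclosed.** Study Design states the mismatch of levels, calls the design nonrandomized and refers to a source on its drawbacks, and the Discussion concedes purposive selection. This stands in part. Those statements concern confounding through how the TAs were chosen. None says that one TA per arm makes arm and TA-specific change inseparable, or that the CIs omit that level.

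**Listing TA is a slip of wording.** This stands. The next clause of Analysis names village size as the fixed effect to be included, and Adjustment for Covariates omits TA. A reader might infer that the plan depends on an impossible adjustment that would spoil the estimates. It does not: the term is redundant, and the fault is an inconsistency.

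**The shortfall in precision is unknown.** This also stands. A reader might take the SE implied by the MDE (13.6/2.80 = 4.85 points), add an assumed TA-change SD of 1 to 5 points, and report a corrected MDE of 14.2 to 24.0 points. The documents do not support that range, for three reasons:

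- The 4.85 points come from a single-round end-line comparison, whereas between-round TA change belongs to a difference-in-difference. If the rounds were independent, that SE would be nearer 4.85 × √2 = 6.9 points. An SD of 3 points would then give a false-positive rate of about 10%, against 14% with the single-round SE.
- The planned test is a mixed logit interaction reported as an odds ratio, not a risk difference.
- The base is 67%, but Table 2 gives coverage with any facility of 1 − 36/600 = 94% (control), 1 − 15/400 = 96% (CLTS+CG) and 1 − 9/400 = 98% (CLTS). A rise of 13.6 points or more has no room there.

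**The evidence of TA-wide shifts is thin.** This is fair. The remark on reversion gives no timing or extent, and the NGO work concerned water. Both make TA-level change plausible but do not measure it.

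**Conclusion.** The concern holds in this form: arm and TA coincide, and the planned CIs and the 13.6-point MDE leave out a level of variation that these data cannot estimate. The CIs are valid for how differently the three study TAs changed. As statements about CLTS or CLTS+CG they are too narrow unless TA-specific change is zero.

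How far too narrow is not known. The coverage figures (94% to 74% for an s/SE ratio of 0.25 to 1) rest on an assumed ratio and on TA changes that are independent with equal SD. They show direction and sensitivity and are not a corrected result. The MDE arithmetic is right on its own assumptions.

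The claim about the W4E program area reaches beyond the three TAs studied; Study Design itself mentions 5 TAs scheduled for the second programme year and 3 for the third. The point should be fixed. It changes what the trial may conclude, not the estimate.

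**What to change.** 1. **Analysis.** Delete TA from the design variables, so that the section agrees with Adjustment for Covariates. State that arm and TA coincide and that the CIs exclude TA-level variation. Add a tipping-point analysis on the scale of the planned difference-in-difference. For each of the three contrasts, give the TA-specific change that would bring the CI to the null. For binary outcomes this is the distance from the nearer confidence limit to zero on the log-odds scale.
2. **Sample Size.** State that the MDE and 80% power assume no TA-specific change. Any illustrative range should be built for the difference-in-difference estimator at the observed 94% to 98% baseline, with the SD of TA change labelled as assumed.
3. **Abstract Conclusions, Discussion and Conclusion.** Add one TA per arm to the limitations, and word the conclusion as the difference in change between the three study TAs.

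End line was completed in March to April 2024, so TAs cannot be added. The cost is a few sentences, a few lines of analysis and a weaker claim.

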**Figure 2 figure2:**
[figure not shown]
Study CONSORT (Consolidated Standards of Reporting Trials) diagram for a controlled before-and-after trial to assess the effectiveness of two interventions (CLTS only and CLTS+CG) on rural sanitation coverage and use in Chiradzulu District, Malawi. CG: care group; CLTS: community-led total sanitation.

### Sample Size

Sample size calculations were based on the minimum detectable effect (MDE) to assess changes in sanitation coverage, the primary outcome measure, at the project end line. Data for all parameters used in sample size calculations were drawn from the baseline survey conducted by World Vision before the implementation of the W4E project between January and April 2021. For the MDE calculation, we assumed a 2-tailed test with a significance level of 0.05 and a power of 0.8. We assumed a conservative intracluster coefficient of 0.1 [30]. As baseline data indicates that the average percentage of households with at least unimproved sanitation coverage across Chiradzulu District was 67%, power calculations assumed a total enrollment of 20 intervention clusters in each TA receiving interventions and 30 clusters selected from the control arm of the study. Assuming an average of 20 households surveyed per selected cluster results in an MDE of 0.136 or an average difference of 13.6 percentage points in sanitation coverage (relative change in coverage of 19%) between either arm of intervention clusters and the control cluster. Therefore, the study aims to recruit a total of 1400 households (CLTS+CG: n=400; CLTS only: n=400; Control: n=600; Figure 2) at each data collection round.

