### Study Outcomes

The primary outcome is sanitation coverage. Secondary outcomes include basic sanitation coverage, sanitation use, sanitation-related quality of life, latrine quality, presence of a handwashing facility, handwashing behavior, and safe disposal of child feces (Multimedia Appendix 3).

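### The 13.6-point minimum detectable effect assumes 67% coverage, but the trial's own baseline is 94–98%, leaving little upward room and low power for realistic gains

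*Protocol article*

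**What the plan says.** Under Study Outcomes, "The primary outcome is sanitation coverage". The Sample Size section specifies the level of service used for power: "As baseline data indicates that the average percentage of households with at least unimproved sanitation coverage across Chiradzulu District was 67" per cent. Its parameters were "drawn from the baseline survey conducted by World Vision before the implementation of the W4E project between January and April 2021". The other inputs are that "we assumed a 2-tailed test with a significance level of 0.05 and a power of 0.8" and that "We assumed a conservative intracluster coefficient of 0.1". There are 20 villages in each intervention arm, 30 in control, and 20 households per village. The result is an MDE of 0.136 for either intervention arm against control.

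The Analysis section takes the arm-by-round interaction (a difference-in-difference) as the primary effect measure, from a mixed logistic model.

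Table 2 reports the trial's own baseline of May–June 2023. Households with no facility number 36/600 (control), 15/400 (CLTS+CG) and 9/400 (CLTS). The Abstract reports the baseline differently: "Sanitation coverage also varied among the study arms at baseline as 83% of households had access to unimproved sanitation in the CLTS group", with 70% for CLTS+CG and 81% for control.

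**The concern.** At the level used for power, every household with any facility counts as covered. Table 2 therefore puts the trial population near the ceiling, far from 67%. The article prints both sets of figures, and its Discussion calls coverage relatively high, but it does not revisit the MDE.

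What is at stake is how the result will be read. The objectives are about improving coverage. A reader who relies on the Sample Size section would take a non-significant result as evidence against CLTS or care groups, when even near-complete success would usually miss significance.

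The Abstract makes the ceiling hard to see. Its 83%, 70% and 81% are Table 2's 'Unimproved' row alone and leave out households with better facilities. CLTS+CG then looks worst covered, although it has the most households in the basic and limited categories combined: 107/400 (26.8%), against 58/400 (14.5%) in CLTS and 81/600 (13.5%) in control.

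**Working it through.** **1. Reproduce the stated MDE.** Inputs from Sample Size: ICC 0.1, 20 households per village, 600 control and 400 intervention households, two-sided 0.05, power 0.80.

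- Design effect = 1 + (20 − 1) × 0.1 = 2.9.
- Effective sizes: 600/2.9 = 206.9 and 400/2.9 = 137.9.
- Power = Φ[(d − 1.96·s0)/s1], where s0 is the standard error under the pooled proportion and s1 the unpooled one.
- For 67% v 80.6%: pooled proportion 0.7244, s0 = 0.0491, s1 = 0.0469, so (0.136 − 0.0963)/0.0469 = 0.847 and power = 0.801.
- Solving for exactly 80% gives 0.1358. The stated 0.136 is confirmed as an end-line comparison of two proportions.

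**2. Coverage at the same level in Table 2** (basic + limited + unimproved).

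| Arm | Covered | Coverage | Largest possible rise |
|---|---|---|---|
| Control | (26+55+483)/600 = 564/600 | 94.0% | 6.0 points |
| CLTS+CG | (43+64+278)/400 = 385/400 | 96.25% | 3.75 points |
| CLTS | (28+30+333)/400 = 391/400 | 97.75% | 2.25 points |
| All | 1340/1400 | 95.7% | 4.3 points |

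**3. The plan's formula at the observed control level of 94%.**

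- Upward MDE: 5.6 points, so the intervention arm must reach about 99.6%.
- 94% v 97%: s0 = 0.0235, s1 = 0.0220, (0.03 − 0.0461)/0.0220 = −0.73, power 0.23.
- 94% v 98%: power 0.42. 94% v 99%: power 0.66.

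**4. Difference-in-difference, the planned effect measure.** For each arm and round, variance = p(1 − p) × 2.9/n, with correlation r between the two rounds' village means. The documents give no r. I assume a range from 0 to 0.69; the upper end is 20 × 0.1/2.9, for the same villages with fully stable village effects and freshly sampled households. Control stays at 94% and the intervention arm reaches 99.9%.

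| Contrast | Gain | SE (r = 0 / 0.69) | Power (r = 0 / 0.69) |
|---|---|---|---|
| CLTS+CG v control | 3.65 points | 0.0285 / 0.0194 | 25% / 47% |
| CLTS v control | 2.15 points | 0.0267 / 0.0170 | 12% / 24% |

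**5. The other direction: control declines, intervention arm unchanged.** Solve x = (1.960 + 0.842) × SE(x), with control falling from 94% to 94% − x.

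- CLTS+CG: x = 10.7 points (r = 0) to 5.8 points (r = 0.69).
- CLTS: x = 9.9 points (r = 0) to 5.3 points (r = 0.69).

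**6. Basic sanitation coverage, a planned secondary outcome.** From the control baseline of 26/600 = 4.3%, the same end-line formula gives an MDE of about 8.4 points.

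**The case against.** A reader might infer that the MDE exceeds any attainable effect, so that the primary comparison cannot succeed. The documents do not support that. The 13.6 points is valid at 67%; the MDE shrinks as coverage nears 100%, and at 94% it is about 5.6 points, just inside control's 6.0-point headroom. A difference-in-difference also credits protection against loss. The article makes loss plausible: the Introduction says Malawian communities find full coverage hard to maintain, and the Discussion says that pits without slabs may collapse in the rains and that other areas of the district have gone back to open defecation. This stands, and step 5 gives its size.

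A reader might also take "OD rates in Malawi and Chiradzulu District are 6% and 7%, respectively" as contradicting 67%. It does not: open defecation is a behaviour, 67% is household coverage, and Table 2 shows that latrines are shared.

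Nor should the Abstract be read as concealment. It does use the word unimproved, Table 2 prints every category, and the Discussion acknowledges high coverage. It is a labelling error.

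Two technical objections have weight. The power figures use a normal approximation on risk differences close to 100%, whereas the plan fits a mixed logistic model, so they are approximate. And the ICC of 0.1 is described as conservative. At an assumed ICC of 0.01, end-line power rises to about 51% for 94% v 97% and 82% for 94% v 98%; no ICC changes the headroom.

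Finally, the full outcome definition is in Multimedia Appendix 3, which is not shown. If it adds conditions to the Sample Size wording, the headroom would differ.

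**Conclusion.** The point holds in a limited form. The arithmetic behind 13.6 points is sound, but its 67% input does not match the trial's baseline of 94.0%, 96.25% and 97.75%, so the stated MDE does not apply to this population. Room for improvement is 2.25 to 6.0 points. At the plan's ICC, power for realistic gains is low: 23–42% at end line for gains of 3 to 4 points from 94%, and 12–47% by difference-in-difference even if an intervention arm reaches 99.9% with control flat. The trial keeps 80% power against a control decline of about 6–11 points (v CLTS+CG) or 5–10 points (v CLTS) with the intervention arm unchanged. A null on coverage would therefore say little about gains, but the outcome is not without use.

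These figures assume the coverage definition in Sample Size, ICC 0.1, 20 households per village and, for the difference-in-difference, a between-round correlation of 0 to 0.69. The mislabelled Abstract figures are a separate, smaller error that needs no assumption.

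**What to change.** - **Sample Size:** keep the a priori calculation as the record of how the sample was set; do not overwrite it. Add the MDE at the observed baseline (about 5.6 points from 94% on the same formula) and say that 13.6 points does not apply to this population.
- **Interpretation:** state that gains are capped at 2.25 points (CLTS) and 3.75 points (CLTS+CG), that a null is uninformative about gains, and what size of control decline the design can detect.
- **Basic sanitation coverage:** report an MDE for this planned secondary outcome (about 8.4 points from 4.3%), labelled as added after baseline. Leave the registered primary outcome unchanged. The end-line survey took place in March–April 2024, so promoting another outcome now would be open to the charge of data-informed re-prioritisation.
- **Abstract:** give sanitation coverage as 97.8% (CLTS), 96.3% (CLTS+CG) and 94.0% (control), or label 83%, 70% and 81% as the 'unimproved' category only.

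The cost is wording and a short recalculation. No new data are needed, and neither the sample nor the primary outcome changes. The stated power becomes less favourable.
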